### 3.4. Study period

13 September 2021 (week 37, 2021- vaccine booster roll-out started) to extract date. For hospitalisation and deaths an earlier date for samples included will be used to allow sufficient time for capture of these events.

### 3.5. Exposure

Vaccination status will be subdivided as follows.

- I. Unvaccinated: no vaccine received
- II. Primary BNT162b2 course followed by a BNT162b2 booster:
  - a. 0-1 days since booster (PF/MD booster combined)
  - b. 2-6 since booster (PF/MD booster combined)
  - c. 7-13 post booster
  - d. 14-34 days post booster
  - e. 35-69 post booster
  - f. 70+days post booster
- III. Primary ChAdOx1-S course followed by a BNT162b2 booster:
  - a. 0-1 days since booster (PF/MD booster combined)
  - b. 2-6 since booster (PF/MD booster combined)
  - c. 7-13 post booster
  - d. 14-34 days post booster
  - e. 35-69 post booster
- IV. Primary BNT162b2 course followed by a half dose Moderna booster:
  - a. 7-13 days since booster

- b. 14 days + since booster
- V. Primary ChAdOx1-S course followed by a half dose Moderna booster:
  - a. 7-13 days since booster
  - b. 14 days + since booster
- VI. Primary BNT162b2 course given at least 175 days before AND not followed by a booster
- VII. Primary ChAdOx1-S course given at least 175 days before AND not followed by a booster

The first few days following the booster could serve as a useful comparator period to estimate the relative VE of the booster to 2 doses as these may reflect a period before the booster has any effectiveness. This may help with possible differences between populations who receive booster doses compared to those who don't. To avoid possible bias due to testing due to any reactogenicity the first 24 hours following the booster may need to be excluded as has been seen with previous doses. The exact days to be used will be assessed visually by plotting the distribution of cases and controls by days since booster. Comparison will only be made within those receiving the same booster.

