## 1. Background

This is the protocol for the assessing the effectiveness of COVID-19 booster doses in England using community testing through Pillar 2 and the test negative case control design. Many of the methods follow those used recently to assess waning of effectiveness for ChAdOx1-S (Vaxzevria, AstraZeneca) and Pfizer-BioNTech (BNT162b2/ Comirnaty®) vaccines (1).

In the UK, COVID-19 booster vaccines were introduced on 14 September 2021. The UK Joint Committee on Vaccination and Immunisation (JCVI) recommended either a BNT162b2 or a half dose (50µg) of mRNA-1273 (Spikevax, Moderna) vaccine to be given as a booster dose no earlier than 6 months after completion of the primary vaccine course (2).

The initial booster programme is currently for all adults over 50 and those 16-49 years with underlying health conditions that put them at higher risk of severe COVID-19, adult carers and adult household contacts (aged 16 or over) of immunosuppressed individuals, and healthcare workers. On the 30 November 2021 the booster vaccine programme was rolled out to all individual's aged 18 years and over.

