## 7. Changes to the analysis plan between version 2.1 (the final version before the first booster analysis) and 2.2 (current version)

| Change                                                                            | date       | Reason                                                                                                                                                              |
|-----------------------------------------------------------------------------------|------------|---------------------------------------------------------------------------------------------------------------------------------------------------------------------|
| Addition of 18-49 analysis                                                        | 06/12/2021 | This age group was added to general recommendation for boosting                                                                                                     |
| Maximum of 1 test negative in the follow-up period                                | 06/12/2021 | As the booster period is quite short using up to 4 random negatives is not necessary and using 1 helps ensure independence.                                         |
| Addition of post booster intervals of 14-34,35-69 and 70+ days post vaccination   | 06/12/2021 | More time has now passed to allow potential waning to be assessed.                                                                                                  |
| Change from 140+ days to 175+ days as the comparator follow-up period post dose 2 | 06/12/2021 | The vast majority of boosters given at the time of the study were from 175+ days so this represents a better estimate of the waned post dose 2 level of protection. |

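### Section 3.5 gives ChAdOx1-S primed, BNT162b2 boosted people no exposure category from day 70 after the booster

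*Protocol*

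**What the plan says.** Section 3.5 of the protocol lists the levels of vaccination status. Group II (BNT162b2 primary course, BNT162b2 booster) has six time bands, the last being "f. 70+days post booster". The next group, "III. Primary ChAdOx1-S course followed by a BNT162b2 booster", has five, and its last is "e. 35-69 post booster". The two Moderna groups, IV and V, each end in "b. 14 days + since booster". Their first week is taken up in the pooled early bands, the first of which is labelled "0-1 days since booster (PF/MD booster combined)".

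The change table in section 7 records, for 06/12/2021, "Addition of post booster intervals of 14-34,35-69 and 70+ days post vaccination", with the reason "More time has now passed to allow potential waning to be assessed". It names no schedule.

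**The concern.** Groups II and III receive the same booster and differ only in the primary course, yet one list of bands is open at the top and the other is closed. Section 3.9 enters vaccination status as the independent variable in the logistic model, so every eligible test needs a level. A group III test from day 70 onward has none. Whoever codes the analysis must drop it, put it in the 35-69 band, or create a level that the protocol does not define, and the protocol does not say which.

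The primary objectives ask for relative VE of each booster by primary course. At stake is the late follow-up of one of the two BNT162b2-booster schedules.

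**Working it through.** The protocol states no figure to reproduce here. The check has two parts: which days the bands cover, and whether the uncovered days could already occur.

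**Coverage of days since booster, as listed in section 3.5**

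| Group | Bands | Last band | Days 0-83 left uncovered |
|---|---|---|---|
| II | 0-1, 2-6, 7-13, 14-34, 35-69, 70+ | open | none |
| III | 0-1, 2-6, 7-13, 14-34, 35-69 | closed | 70-83 |
| IV, V | pooled 0-1 and 2-6, then 7-13, 14+ | open | none |

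Group III is the only booster schedule with a closed last band.

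**Is such a person eligible, and could another category take the test?**
- The vaccination data paragraph of section 3.2 admits people with three doses at onset and at least 175 days from dose 2 to dose 3. A group III recipient at day 70 can meet both conditions.
- Group VII covers the ChAdOx1-S primary course without a booster, so it does not apply. Groups I, II, IV, V and VI do not fit either.
- Neither section 3.4 nor section 3.9 sets an upper limit on time since booster. The study period runs to the extract date.

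**Could day 70 be reached?**

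Inputs: "In the UK, COVID-19 booster vaccines were introduced on 14 September 2021" (section 1); the revision date 06/12/2021 (section 7); the 175-day rule (section 3.2); repeats about every three weeks (section 3.8).

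- First date on which day 70 can occur: 14 September + 70 days = 23 November 2021, before the revision.
- Longest time since booster at the revision: 14 September to 6 December = 83 days.
- Latest booster date at day 70 by the revision: 6 December - 70 days = 27 September.
- Affected booster dates at the revision: 14 to 27 September inclusive = 14 calendar dates, at days 70-83. Someone boosted on 27 September is at day 70 exactly.
- Latest possible dose 2 for these people: 14 September - 175 days = 23 March 2021, to 27 September - 175 days = 5 April 2021.
- Growth if the bands stay as written: each 21-day step adds 21 booster dates. One step after the revision (27 December) the longest time since booster is 83 + 21 = 104 days, and 104 - 69 = 35 booster dates are affected.

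With a 70+ band added to group III, the uncovered days in the range 0-83 fall from 14 to 0.

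**The case against.** The strongest reply is that few ChAdOx1-S primed people may have reached day 70 by early December 2021. They needed dose 2 by 23 March to 5 April 2021 at the latest, and the protocol gives no counts. The bands might also be extended later, as they were on 06/12/2021. For hospitalisation and death, section 3.4 uses an earlier sample cut-off, so the gap is smaller for those outcomes. All of this stands as a limit on size. It does not explain the gap: sparse data would call for an open 35+ band, as the Moderna groups have from day 14. A deliberate restriction to day 69 would be legitimate but would have to be stated.

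A reader might also infer that the single Moderna band from day 14 is the same fault, or that it spoils a comparison between brands. The protocol does not support that. Groups IV and V are fully classified. The objectives compare each booster with two doses, no doses or the first days after a booster, and none sets one booster against another. Pooling a second booster whose counts are not given is a reasonable choice for precision.

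Nor does the point rest on the difference between the change table and section 3.5. A change log does not govern the current text, and the table does not say that the 70+ band was meant for every schedule. The gap follows from section 3.5 alone.

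**Conclusion.** The omission is real and confined to group III. Eligible tests with onset 70 or more days after a BNT162b2 booster in ChAdOx1-S primed people have no exposure category, so relative VE for that schedule cannot be estimated past day 69.

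The size can be given only in calendar terms: 14 booster dates at the 06/12/2021 revision, widening with each extract. This takes 14 September as the first booster date and counts onsets up to the stated date; actual extracts would lag somewhat. Growth after the revision assumes unchanged bands and steps of about 21 days. The number of people cannot be derived from the protocol.

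It would go too far to say that the primary objectives fail for this schedule or that a reported estimate is biased. If the late tests are simply left out, the estimates for 7-13, 14-34 and 35-69 days remain defined. It would also overstate matters to call booster waning a formal objective: it appears only as the reason for the new bands in section 7.

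**What to change.** In section 3.5, add a sixth band to group III, f. 70+ days post booster, to match group II. If late data are too sparse to report, open the last band of group III as 35+ days instead, so that every eligible test has a level; that figure would then no longer line up with the 35-69 band of group II.

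The change is one line in the exposure list and the matching line of code, with no new data. The cost is that the late band may hold few cases and carry a wide confidence interval. Groups IV and V need no change on this account.

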### 3.6. Outcomes

- Individuals testing positive for SARS-CoV-2 on PCR who reported symptoms within the preceding 10 days
- Individuals testing positive for SARS-CoV-2 on PCR who report symptoms and have a hospital admission from ECDS within 14 days of testing.
- Individuals testing positive for SARS-CoV-2 on PCR who report symptoms and die within 28 days of testing.

### 3.7. Data management

Data will be managed using SQL management studio and analysed using Stata. Surveillance of covid-19 testing and vaccination is undertaken under Regulation 3 of The Health Service (Control of Patient Information) Regulations 2002 to collect confidential patient information ([www.legislation.gov.uk/uksi/2002/1438/regulation/3/made](http://www.legislation.gov.uk/uksi/2002/1438/regulation/3/made)) under Sections 3(i) (a) to (c), 3(i)(d) (i) and (ii) and 3(3). The study protocol was subject to an internal review by the Public Health England Research Ethics and Governance Group and was found to be fully compliant with all regulatory requirements. As no regulatory issues were identified, and ethical review is not a requirement for this type of work, it was decided that a full ethical review would not be necessary.

### 3.8. Sample size and analysis frequency

Analysis will be done approximately 5 weeks after the booster program has been introduced to allow time for data to accrue to allow good precision of VE estimates. Analysis will be repeated at approximately 3 week intervals and later analyses will allow inclusion of hospitalisations and then deaths. Initial analyses will not include these end points.

### 3.9. Statistical analysis

We will use a test-negative case-control design to estimate vaccine effectiveness of a booster dose of BNT162b2 vaccine against PCR-confirmed symptomatic disease, hospitalisation and death. Analysis will be by logistic regression with the PCR test result as the dependent variable where those

testing positive are cases and those testing negative controls. Vaccination status will include as an independent variable and effectiveness defined as 1- odds of vaccination in cases/odds of vaccination in controls. Estimates will be reported with 95% confidence intervals. Analyses will stratified by which primary doses had been received.

Vaccine effectiveness will be adjusted in logistic regression models for:

- age (5 year bands)
- sex
- index of multiple deprivation (quintile)
- ethnic group
- care home residence status
- geographic region (nhs region)
- period (calendar week of onset)
- health and social care worker status
- clinical risk group status
- clinically extremely vulnerable
- severely immunosuppressed
- previously testing positive

These factors will all be considered potential confounders so will be included in all models.

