## 2. Objectives

### 2.1. Aim

To estimate the effectiveness of COVID-19 booster vaccines against covid-19 related symptoms, hospitalisation and death in adults aged 18-49 years and 50 years and older

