### 2.2. Primary objectives

- I. Relative VE of each booster vaccine by primary course vaccine type against symptomatic disease compared to 2 doses
- II. Relative VE of each booster vaccine by primary course vaccine type against hospitalisation following symptomatic disease compared to 2 doses
- III. Relative VE of each booster vaccine by primary course vaccine type against death following symptomatic disease compared to 2 doses

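### For death, one ordinary 12-factor logistic model on a single set of time-since-booster bands gives no finite VE and no 95% interval in a band without deaths, a risk greatest at ages 18-49

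*Protocol*

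**What the plan says.** Section 3.9 of the protocol names logistic regression as the method for VE "against PCR-confirmed symptomatic disease, hospitalisation and death", with 95% confidence intervals. It states: "Analyses will stratified by which primary doses had been received". It lists 12 adjustment factors, including age in 5-year bands and calendar week of onset, and says of them: "These factors will all be considered potential confounders so will be included in all models". It makes no exception by outcome or age group.

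The other parts of the point come from other sections:

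- Section 2.2, objective III: "Relative VE of each booster vaccine by primary course vaccine type against death following symptomatic disease compared to 2 doses".
- Section 2.1 covers "hospitalisation and death in adults aged 18-49 years and 50 years and older". Section 7 records that the 18-49 analysis was added on 6 December 2021 (section 3.3 still names only those aged 50 and over).
- Section 3.5 begins "Vaccination status will be subdivided as follows" and gives one classification for every outcome. After a BNT162b2 primary course there are six BNT162b2-booster bands and two Moderna bands; after ChAdOx1-S there are five and two. The Moderna groups end in one open band, "b. 14 days + since booster".
- Section 3.8 says that "later analyses will allow inclusion of hospitalisations and then deaths", without giving a count at which they enter. Section 3.4 uses an earlier sample cut-off for hospitalisation and death.

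**The concern.** Read together, these sections apply the full model, by age group and primary course, to the rarest outcome on the same fine bands as symptomatic disease. A band with no deaths has no finite maximum-likelihood odds ratio and no Wald interval: the estimate runs off towards VE 100%, or the level is dropped. Empty bands are most likely where the booster protects best.

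At very low counts there is a second effect. Only bands in which at least one death happened to occur yield a number, so the reported set leans towards weaker protection. Since the reports go to JCVI (section 5), sparse data could then be read as poor protection, and the analyst would have to choose another method after seeing which bands are empty.

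**Working it through.** The protocol states no event count, sample size or power, so there is no planned figure to reproduce. All death counts and exposure shares below are assumptions.

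**1. Size of the model.** Parameters are levels minus one. Levels of ethnic group (5 to 18), region (7 to 9), age (7 to 9) and week (9 to 13) are assumed. From 13 September to 6 December 2021 is 13 calendar weeks; 9 allows for the earlier cut-off for deaths.

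- Low: age 6 + sex 1 + deprivation 4 + ethnicity 4 + care home 1 + region 6 + week 8 + five yes/no factors 5 = 35.
- High: 8 + 1 + 4 + 17 + 1 + 8 + 12 + 5 = 56.
- Vaccination adds 7 (ChAdOx1-S stratum, relative VE) to 9 (BNT162b2 stratum with the unvaccinated).
- Total: 35 + 7 = 42 to 56 + 9 = 65 per model.

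**2. Chance of an empty band.** Let D be the deaths in the two-dose reference group and r the ratio of band controls to reference controls. Expected deaths in the band are E = D × r × (1 − rVE), and P(no deaths) = exp(−E).

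| D | r | rVE | E | P(no deaths) |
|---|---|---|---|---|
| 20 | 0.2 | 90% | 0.40 | 67% |
| 50 | 0.2 | 90% | 1.0 | 37% |
| 50 | 0.05 | 90% | 0.25 | 78% |
| 50 | 0.2 | 80% | 2.0 | 14% |
| 300 | 0.2 | 90% | 6.0 | below 1% |

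**3. Why sparse estimates lean low.** With D = 20 and r = 0.2, the smallest non-zero count, one death, gives a crude odds ratio of 1/(20 × 0.2) = 0.25, so VE 75%. Under a true 90%, that band can show 75% or less, or nothing.

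**4. An empty band still carries information.** With the reference count treated as fixed, the upper 95% limit for a count of zero is −ln(0.025) = 3.69. For D = 50 and r = 0.2, the crude lower VE limit is 1 − 3.69/10 = 63%. For D = 20 it is 1 − 3.69/4 = 8%. Neither should be reported as 100%, and neither should be dropped.

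**5. Simulation of the stated fit.** 49 parameters, 6,000 controls and 150 runs per setting. Assumed control shares: 45% two-dose, 17% at 14-34 days, 13% at 35-69 and 4% at 70+, the rest in early and Moderna bands. True log odds ratio −2.30 (VE 90%). Covariate effects are assumed. The last three columns refer to runs in which the 14-34 day band had at least one death.

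| Deaths | 14-34 band empty | 70+ band empty | Mean log OR (as VE) | Median SE | Wald coverage |
|---|---|---|---|---|---|
| 20 | 56% | 88% | −1.59 (80%) | 1.06 | 91% |
| 50 | 20% | 70% | −2.23 (89%) | 0.74 | 98% |
| 100 | 4% | 49% | −2.40 (91%) | 0.60 | 95% |
| 250 | 0% | 13% | −2.44 (91%) | 0.40 | 97% |
| 500 | 0% | 2% | −2.32 (90%) | 0.28 | 95% |

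A separate simulation with 46 parameters and other assumed inputs found the 14-34 day band empty in 72%, 23% and 7% of runs at 20, 50 and 100 deaths. At 20 deaths the median VE was 79% among estimable runs, against 88% with Firth penalised likelihood. From about 50 deaths the ordinary fit gave a median of 88-89%, and Firth brought no gain.

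As a guide to imprecision at 50 deaths: −2.30 ± 1.96 × 0.74 is −3.75 to −0.85, or VE 57% to 98%.

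**6. Dates.** Someone boosted on 30 November 2021 reaches day 14 on 14 December, day 35 on 4 January 2022 and day 70 on 8 February 2022, before the 28 days needed to capture a death. Until then, the later bands at ages 18-49 can be filled only by those eligible from September (section 1: clinical risk, carers, household contacts, healthcare workers).

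**The case against.** Several parts of the opposing case stand. Keeping one pre-named confounder set in all models is a sound guard against selective adjustment. A statistical analysis plan that is not shown may contain a sparse-data rule, so its absence here is no finding. Deaths enter only later analyses (section 3.8), analyses repeat about every 3 weeks so an empty band may fill, Moderna boosters already have only two bands, and the ChAdOx1-S then BNT162b2 group has no 70+ day band. The sentence on confounders does not itself fix the bands or name the 18-49 group; that follows only when section 3.9 is read with 2.1, 2.2, 3.5 and 7.

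A reader might go further and infer that 42 to 65 parameters make the whole death analysis over-parameterised, so that every remaining estimate is untrustworthy and a trigger of 10 deaths per parameter (420 to 650 per model) is needed. The documents do not support this. They give no death counts, and at 100 deaths (100/49, about 2 per parameter) the 14-34 day estimates were close to the truth with 95% coverage. Such a trigger, with coarser calendar periods, would give up time adjustment during a fast rollout where the stated model works.

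A reader might also extend the point to hospitalisation or the Moderna groups in general. No calculation here supports that.

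What the objections leave untouched is that the method named cannot give the promised interval in a band with no deaths. Deferring deaths does not cure this, because no count is set and the model is unchanged when they enter.

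**Conclusion.** The point holds in a limited form. For death, and mainly at ages 18-49, the named fit yields no finite VE and no 95% interval in any band without deaths. At about 20 deaths per age-by-primary-course stratum, the 14-34 day band was empty in more than half of runs, and the estimates obtained centred on about 80% when the truth was 90%. From about 50 deaths, non-empty bands are imprecise but not materially biased.

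That last result was measured on the 14-34 day band. What matters is the expected number of deaths in the band, so a small band such as 70+ days, still empty in 70% of runs at 50 deaths, needs more. All sizes depend on assumed counts, exposure shares and covariate effects. If strata hold several hundred deaths, the problem is largely confined to the smallest bands.

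**What to change.** State in section 3.9 that, for death strata with a zero-event or very sparse band:

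- the same 12-factor model, including calendar week, is fitted by Firth penalised likelihood with profile-likelihood intervals;
- a pooled 14+ day band, as section 3.5 already uses for the Moderna booster, is reported alongside the separate bands;
- any band with no deaths is reported with its event counts and a lower confidence limit for VE, and is neither dropped nor shown as 100%.

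Keep the full confounder set. No events-per-parameter trigger is needed. The cost is some wording, an alternative fitting command, slight shrinkage of large effects and a little more analysis work.
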